## I. Purpose of the Study and Background

### IIa. Purpose of the Study

Case management (CM) and care coordination (CC) programs were designed to partner with high-cost, complex, at-risk consumers to facilitate health care access and decisions that can have a dramatic impact on the quality and affordability of the consumer's health care. CM programs leverage a collaborative process of assessment, planning, facilitation and advocacy for options and services to meet an individual's health needs through communication and available resources to promote quality cost-effective outcomes. CC is defined as a process of improving communication among the various medical professionals with whom patients come in contact and between these professionals and their patients (and their families). In general, CM and CC programs show modest gains in quality of care. However, programs with strong transitional care interventions that target high risk patients were found to lower hospital admissions.

The current quality improvement study (QIS) was designed to determine if case management and care coordination (CM/CC) provided to commercially insured members identified via a proprietary administrative algorithms as being either 1) high-need, high-cost (i.e., identification in the top 5% of spend in the previous year and in the next 12 months) or 2) high inpatient risk for admission would significantly impact rates of acute inpatient admissions, 30 day all-cause re-admissions, outpatient emergency room (ER) visits, primary care physician (PCP) visits, and specialist physician visits. The entire intervention group will be eligible for the CM/CC program and will be compared to a control group which will only receive the CM/CC program if they are 1) identified as high risk for readmission upon discharge from the hospital, 2) are self-referred, or 3) are directly referred to the program by their physician.

The goal of the QIS is to 1) identify if the expansion of the CM/CC program to members identified as being at high risk would improve selected health outcomes, and 2) if the addition of a community health worker to the CM/CC model would improve selected health outcomes. This is important because the identified population is at high risk for future hospitalization. The two specific aims of the current QIS include:

- a. *Challenge the current state via a pragmatic randomized controlled trial with health plan members as the unit of randomization.* Randomly allocate approximately 705,000 high-risk members into two groups over a four-year period. Compare rates of utilization including acute inpatient admissions, readmissions, ER visits, PCP visits, and specialist visits. This knowledge will allow decision makers to minimize uncertainty as they evaluate opportunities to expand the program.
- b. *Investigate the comparative effectiveness of the approaches to improve health outcomes.* The identification of an improved approach to the expansion of the CM/CC program could lead to reduced complications and improved health outcomes.

The long-term aims of the proposed study are to disseminate the study's findings. The authors anticipate that the communication of positive study results would result in the expansion of the CM/CC model to the entire high-need, high-cost population and ultimately, lead to improved health outcomes for members with high costs and utilization.

### II.b. Background

Each day individuals make decisions that impact their health and health care costs. The Centers for Disease Control and Prevention has identified that 50 percent of an individual's health status is determined by behavior — not genetics, environment or access. In response to these and similar findings, the CM/CC solution was designed by UHG as a clinically integrated and consumer-focused program of assessment, planning, facilitation and advocacy that leverages all available resources, including the health care team, the payer, and the community.

As a first step, it is important to define the rubric within which the programs of interest fall. The assignment of a rubric allows you to understand whether the intervention is tied to an event, a diagnosis, or a more general risk

state, as well as the nature and length of the intervention. The CM/CC program includes embedded case management and care coordination components designed to provide short-term and long-term, individualized consumer-centric approaches to managing the unique, costly and complex medical needs of high-risk members.

The Case Management Society of America defines case management (CM) programs as a collaborative process of assessment, planning, facilitation and advocacy for options and services to meet an individual's health needs through communication and available resources to promote quality cost-effective outcomes. This definition encompasses needs for both acute and long-term care. CM programs are generally long-term interventions focused on individuals at high-risk for a specific outcome. The results for geriatric CM programs suggest that they improve quality measures important to vulnerable elders and may reduce hospitalizations among those at highest risk for hospitalization. Within the CM/CC program, a consumer is either enrolled in the Stage 1 program, or the Stage 2 program if the member has a high level of clinical, psychosocial or behavioral needs.

The Stage 1 program focuses on value pillars (right care, right medications, right provider, and right lifestyle) to minimize disease progression and future spend. As part of Stage 1, a Registered Nurse (RN) educates and empowers the consumer to address care opportunities and achieve desired outcomes. Stage 1 cases may require multiple contacts; however, they do not meet criteria for promotion to Stage 2.

The Stage 2 program is available to highly complex members and/or members that require specialty focus by Certified Case Managers. Stage 2 focuses on value pillars to facilitate an appropriate plan of care with physician and consumer to address utilization and clinical issues. A proprietary scoring tool identifies the need for Stage 2 at the time of initial referral to Stage 1 to ensure continuity of management by a single Registered Nurse (RN).

There is no well-established definition for care coordination (CC); however, it is generally defined as a model that involves a process of improving communication among the various medical professionals with whom patients come in contact and between these professionals and the patients themselves (and their families). CC programs are generally short-term interventions focused on a specific event. In general, CC programs show modest gains in quality of care. However, programs with strong transitional care interventions that target high risk patients were found to lower hospital admissions. While there are numerous studies regarding care coordination among Medicare and Medicaid populations, there is a paucity of research focused on the commercially insured population, particularly in the new Individual Public Exchange populations. The CM/CC model also includes embedded care coordination strategies designed to proactively monitor and manage hospitalized patients immediately after their discharge to ensure a safe transition to home. Patients identified for this activity are considered as being at high risk for readmission due to their underlying illness, length of hospitalization, or other complex discharge plan. Consumers are contacted either during or soon after hospital discharge and calls focus on helping the consumer understand his or her discharge instructions, completing medication reconciliation, ensuring the consumer has a follow-up appointment scheduled with a Primary Care Physician (or other appropriate physician), and other interventions that reduce the risk of readmission.

The program involves the process of identifying high-risk or at-risk consumers with acute and chronic healthcare needs that include unexpected catastrophic occurrences, as well as the proactive management of anticipated clinical needs. Members are eligible for the program if they meet one of the following criteria:

- Discharged from an inpatient facility and identified as being at high risk for readmission.
- Identified via physician referral or self-referral as someone who may benefit from care coordination (e.g., experiencing a health issue that requires extra attention)
- Determined to be "high risk" by via other methods.

Case managers encourage wise health care decisions by providing members with expert advice and clinical resources. The member's case manager is available to answer questions about health concerns, educate members on available resources, and inform them of other services that may be helpful. Members experience continuity in their care by connecting with the same case manager from the start of a health event until it is completed.

The scope of the program extends throughout the continuum of care and includes the treating practitioner, consumer (or caregiver) education and engagement, and consumer self-management. The program is designed to support professionally licensed staff to objectively assess, plan, implement, monitor and evaluate the efficiency and appropriateness of care for participating consumers enrolled in the program. RN assessment areas include but are not limited to: current health status and history, treatment plan, resources needed, psychosocial status, health literacy, safety concerns, and functional limitations. Program services are delivered telephonically and through specific consumer mailings. Members with behavioral health needs are referred to appropriate entities per contractual arrangements.

Case management nurses engage both consumers and physicians as needed throughout the case management process. The nurse case manager works directly with the member to support their physician's treatment plan, provide education and coordinate services. The program is designed to complement the physician's treatment plan, reinforce their instructions as provided and offer support to the member to make healthful lifestyle choices. It is not intended to diagnose or treat, and it is not a substitute for the treating physician's professional, medical advice. Periodically, CM/CC Medical Directors may contact the member's physician(s) if it is identified that their patient has been non-adherent with their prescribed treatment regimen or lacks interventions suggested by evidence-based medicine.

In 2014, the CM/CC program was available to commercially insured individuals across lines of business. Approximately 30,000 members participated in the program in 2014. The current study was designed to determine the following:

**Objective 1:** if the CM/CC program would statistically significantly impact health outcomes for commercial members identified as being high-need, high-cost (the QIS is powered to answer this primary objective), and

**Objective 2:** if the addition of a Community Health Worker to the care team would substantially impact health outcomes for Individual Public Exchange members identified as being high-need, high-cost (the QIS is not powered to answer this secondary objective).

It is important to note that throughout the study period, the CM/CC program will continue to be available to all commercial health plan members similar to previous years, including the control group in the current QIS, who are 1) discharged from an inpatient facility and identified as being at high risk for readmission and 2) identified via physician referral or self-referral as someone who may benefit from care coordination.

### **III. Criteria for Subject Selection**

#### **III.a. Baseline Studies**

**III.b. Number of Subjects:** As of July 2015, there were 4.5 million program eligible members. Among the eligible population 102,014 (point prevalence of 2.28%) were identified via a proprietary administrative algorithm as being high-need, high-cost (i.e., identification in the top five percent of spend and utilization in year 1 and year 2, based on member characteristics in Year 1). Since the inclusion algorithm will be refreshed monthly for 12 months, modelling based on 2014 data suggests that approximately 200,000 unique members will be identified as being at high-need, high-cost, and included in the randomization frame, over the first 12 months of the QIS.

156 **III.c. Gender of the Subjects:** Participants are expected to be 60.1% female.

157  
158 **III.d. Age of the Subjects:** The age range of the sampling frame will be limited to ≥18 years of age.  
159 Participants are expected to have an average age of 47.5.

160  
161 **III. e. Racial and Ethnic Origin:** Racial and Ethnic data are only self-reported for 3.5% of the commercial  
162 population: 20.7% African American, 1.9% American Indian/Alaskan Native, 4.8% Asian, 64.5% White, Non-  
163 Hispanic, 6.6% Hispanic, 0.0% Native Hawaiian or Other Pacific Islander, 1.2% Other, 0.3% Declined to  
164 Answer, and 0.0% Unknown to Member or Uncoded. The distribution of race/ethnicity of the high-need, high-  
165 cost population is expected to mirror the commercial population.

166  
167 **III. f. Inclusion Criteria:** The commercial Fully Insured population members in all states are represented in  
168 the initial population prior to condition identification. This is also inclusive of the Individual Public Exchange  
169 business, part of Health Care Reform, also known as ObamaCare. The age range of the sampling frame will  
170 be 18 or greater years of age. Members must also be actively enrolled in the health plan as of the date of  
171 randomization. Study participants will be identified via proprietary administrative algorithm as being at high-  
172 need, high-cost.

173  
174 **III. g. Exclusion Criteria:** The population sampled will exclude pregnant women, individuals prescribed  
175 medications for infertility, members with evidence of dementing disorders, and members under the age of 18  
176 years old. Members in the following products and plans will also be excluded:

- 177 • legacy ASO groups (populations for which the insurer provides administrative services only),
- 178 • assignment to a clinically activated Accountable Care Organization (ACO)

179  
180  
181 Additional exclusions include members indicated as “do not contact “ for program outreach, , and members not  
182 actively enrolled in the health plan as of the date of randomization.

183  
184 **III. h. Vulnerable Subjects:** The eligible population does not include prison inmates or employees of the  
185 health insurer. The population sampled will exclude pregnant women or individuals prescribed medications for  
186 infertility. Members with evidence of dementing disorders and members under the age of 18 years old will be  
187 excluded from the QIS as a proxy for members with limited cognitive function or decisional incapacity.

## 188 **IV. Methods and Procedures**

### 189 **IV.a. Methods and Procedures**

190  
191  
192 *IV a. 1. Overall Strategy:* The proposed QIS leverages a pragmatic randomized controlled trial design with the  
193 qualified member as the unit of randomization. Pragmatic studies of health services allow healthcare to occur  
194 in natural settings.

195  
196 The primary hypothesis for the **referral** for the **RN Only** model is that the utilization rates among the control  
197 population identified via the standard referral process (i.e., 5-10% of population qualified for Stage 1 and Stage  
198 2 intervention due to high-risk discharge, self-referral, or MD-referral) is not different than the utilization rates  
199 among the intervention population identified by the new referral process (i.e., 100% of population qualified for  
200 the Stage 1 and Stage 2 intervention due to high-need, high-cost status). The current QIS is powered to  
201 answer this primary objective.

202  
203 
$$H_{01}: [Y_{\text{standard referral process with CM/CC}} - Y_{\text{new referral process with CM/CC}}] = 0$$

204  
205 The secondary hypothesis for the **referral** for the expanded **RN+CHW** model is that the utilization rates among  
206 the control population identified via the standard referral process with the enhanced CM/CC model (i.e., 5-10%  
207 of population qualified for Stage 1 or Stage 2 intervention due to high-risk discharge or self-referral or MD-

referral) is not different than the utilization rates among the intervention population identified by the new referral process (i.e., 100% of population qualified for the Stage 1 or Stage 2 intervention due to high-need, high-cost status). The current QIS is not powered to answer this secondary objective.

$$H_{o_2}: [Y_{\text{standard referral process with CM/CC}} - Y_{\text{new PSU referral process with enhanced CM/CC}}] = 0$$

The secondary hypothesis for **inpatient referral** for the **RN Only** is that the utilization rates among the control population identified via the standard referral process with the enhanced CM/CC model (i.e., 5-10% of population qualified for Stage 1 or Stage 2 intervention due to high-risk discharge or self-referral or MD-referral) is not different than the utilization rates among the intervention population identified by the new referral process (i.e., 100% of population qualified for the Stage 1 or Stage 2 intervention due to high risk for PSU status).

$$H_{o_3}: [Y_{\text{standard referral process with CM/CC}} - Y_{\text{new inpatient referral process with CM/CC}}] = 0$$

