#### IV. a. 7. Randomization

Eligible participants will be randomly allocated into two groups. The sponsoring organization will own the randomization process. A unique random number will be generated for each member. The members will be randomly allocated each month to each arm. Restriction (e.g., blocking, stratification, matching) will be leveraged as required.

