#### **CHW CM/CC – Active 11/01/2015 to 7/1/2017**

In selected markets for defined time periods, members randomized to the intervention arm also received an enhanced version of the CM/CC intervention that included in-home care management support from non-clinical Community Health Workers (CHW). A CHW was anticipated to be helpful to ensure that this population understood the general health insurance process, understood the vital importance of establishing a relationship with a Primary Care Physician (PCP), and was assisted with community resources as necessary in order to optimize their health care experience.

In general, the outreach protocol for this enhanced CM/CC intervention mirrored the outreach protocol described previously. However, there were a few differences. The primary difference was that the CHW performed the outreach call and scheduled a home visit with the member if they resided within the CHW's service area. In addition, each member was assigned to a Community Care Team which was comprised of an

on-site CHW, a telephonic RN, and other telephonic specialists as needed. The Community Care Team was accountable for end-to-end integrated person-centered care management of all members to whom they were assigned. All members were assigned to one on-site CHW. Following contact with the CHW, individuals identified with more complex needs were also assigned to a telephonic clinician from the Community Care Team for longitudinal interventions.

As members were enrolled in the program, the Community Care Team also ensured that each member was assigned a PCP, which may have been a specialist, if they had not yet chosen one or wished to change providers. Each member was strongly encouraged and steered towards the optimal use of the PCP as the medical home for community-based health and preventive services. As this link was established, the team involved the PCP in the plan of care (POC) development process and reinforced their treatment plan in accordance with the evidence-based clinical guidelines that form the foundation of the program.

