- Disease: The comparative effectiveness of the program by disease will be evaluated to drive continuous quality improvement and to identify hypotheses for new program offerings. .
- Access to Other Programs: Qualification for other programs will be monitored in order to determine if stratification is necessary by program qualification for other programs since both treatment arms also have access to other care or disease management programs, such as Transplant Resource Services, the End Stage Renal Disease program, the Chronic Kidney Disease program, the Cancer Support program, or the Heart Failure Disease Management program.

*Study Timeline:* The proposed timeline for the QIS includes the following dates & activities:

10/01/2015 IRB Submission  
10/08/2015 Program effective in tech platform  
10/19/2015 Dialer team stages referrals  
11/01/2015 **Intervention begins.** Members start receiving outreach  
12/31/2015 1st monthly operational metrics report available  
01/31/2016 1st monthly operational leading indicator report available  
01/31/2016 1st monthly outcomes report (notifications) available  
05/31/2016 1st monthly outcomes report (claims) available  
06/01/2016 On-site CHW model expanded to 12 states  
12/31/2016 Individual exchange plans end except for NY and VA  
07/01/2017 CHW intervention ends  
10/01/2017 Randomization moved from 50/50 percentage split to 40/60  
09/01/2018 Engagement of inpatient referrals begin  
10/31/2019 **Intervention ends**

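### H02 tests expanded referral and the community health worker together, so it cannot answer Objective 2; the H02 and H03 text also contradicts the protocol's own formulas and arm descriptions

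*Protocol*

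**What the plan says.** Objective 2 in Protocol II.b asks "if the addition of a Community Health Worker to the care team would substantially impact health outcomes for Individual Public Exchange members"; it limits the question to high-need, high-cost members and says the study is not powered for it. Section IV.a.7 states: "Eligible participants will be randomly allocated into two groups". Under the CHW heading in IV.a.8: "In selected markets for defined time periods, members randomized to the intervention arm also received an enhanced version of the CM/CC intervention". The control-group paragraph of IV.a.8 gives controls CM/CC through high-risk discharge, physician referral or self-referral, and mentions no CHW.

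Section IV.a.1 states H02 and H03 each in words and as a formula. In words, the comparator in both is "the control population identified via the standard referral process with the enhanced CM/CC model". In both formulas, the comparator is the standard referral process with plain CM/CC. H03 is introduced as the inpatient-referral hypothesis for the RN Only model, yet its text qualifies the intervention population for the "intervention due to high risk for PSU status".

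Section III.f gives one identification route: "Study participants will be identified via proprietary administrative algorithm as being at high"-need, high-cost. The purpose section and the limitations in IV.a.6 both treat high inpatient risk as a further, separate algorithm.

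**The concern.** An objective about adding a CHW needs a comparison in which the CHW differs and the referral route does not. The H02 formula changes both at once. The H02 text, with the enhanced model on the control side, would remove the CHW difference if taken literally. Neither version isolates the CHW.

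The purpose section makes the CHW question one of the study's two goals, and the sponsor expects positive results to lead to wider use of the model. A rejected H02, read against Objective 2, could be reported as evidence for CHWs when the cause was expanded referral. H03 carries the same control-arm wording and also points to what appears to be the wrong population, so an analyst cannot tell from its text whom to include.

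**Working it through.** The protocol gives no figure to reproduce for H02 or H03. The check sets the statements side by side and writes out what each contrast estimates.

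**1. What H02 estimates.** Let R be the rate ratio for expanded versus standard referral under the RN model, and C the further rate ratio from adding the CHW.

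- Objective 2 asks for C.
- The H02 formula (standard referral with CM/CC against new referral with enhanced CM/CC) estimates R × C.
- The H02 text (enhanced model among controls), with the enhanced model also in the intervention arm, estimates a referral effect only.

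One contrast cannot separate two factors. Suppose H02 gave a rate ratio of 0.926. That fits R = 0.975 with C = 0.95 (0.975 × 0.95 = 0.926), and equally R = 0.926 with C = 1. These values are illustrative only. A larger sample would estimate the product more precisely and still not divide it.

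**2. Whether another randomised contrast supplies C.** There are two randomised groups (IV.a.7). Within the intervention arm, CHW was assigned by market and period, and no randomisation between RN only and RN+CHW is described. Any such comparison is therefore observational.

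**3. Control arm, words against formulas.**

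| Source | Model available to controls |
|---|---|
| H02 and H03 text, IV.a.1 | Enhanced CM/CC |
| H02 and H03 formulas, IV.a.1 | CM/CC |
| Control-group paragraph, IV.a.8 | CM/CC; no CHW mentioned |

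For H03 there are two further conflicts. Its label is RN Only, which rules out an enhanced comparator. The timeline in IV.b ends the CHW intervention on 07/01/2017 and starts engagement of inpatient referrals on 09/01/2018, a gap of 14 months, so the enhanced model was no longer running.

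**4. H03 population.** The heading and formula say inpatient referral, and the purpose section and IV.a.6 describe a separate high-inpatient-risk algorithm. The text says PSU status. PSU is not spelled out where it is used. The H02 formula uses it where the H02 text says high-need, high-cost, and VI.b refers to persistent super utilizers. PSU therefore appears to mean the high-need, high-cost group; this is an inference. III.f admits only that group.

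**5. H02 population.** The text says high-need, high-cost, which agrees with Objective 2. It omits the restriction to exchange members and to CHW markets and dates.

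**The case against.** The best defence is that H02 is introduced as a referral hypothesis for the RN+CHW model, so its formula tests what its label says, and that the protocol twice states it is unpowered. The first point stands: the mismatch is between H02 and Objective 2. It does not remove the problem, because H02 is the only hypothesis offered for that objective. Low power is no answer, since the difficulty is identification. On H03, the intended population can be recovered from the heading, formula and other sections, so the PSU phrase looks like carried-over wording. That is fair, but it still needs correcting. These are not details to leave to an SAP, because the protocol states the hypotheses itself and they conflict.

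A reader might infer more than the documents support:

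- **A specific false CHW effect.** IV.a.3 implies an intention-to-treat effect of 0.20 × 0.20 × 6.5/10.6 = 2.45%, and one might say H02 would show this with a useless CHW. Those are planning inputs for the main program; none are given for exchange members or CHW markets. The CHW also made the outreach call, and a telephonic clinician was assigned to those with more complex needs, so R × C is itself a simplification.
- **Most follow-up horizons being impossible.** The timeline says "Individual exchange plans end except for NY and VA" from 12/31/2016, which leaves 7 months in states added on 06/01/2016. Markets active from 11/01/2015 had up to 14 months, and New York or Virginia, if they were CHW markets, up to 20. The CHW states are not listed, so the share affected is unknown.
- **A confounded exchange-versus-fully-insured comparison.** The CHW description does not say that only exchange members received it. Overlap is plausible but its extent is not shown.
- **H03 simply re-testing H01.** Only the PSU phrase points that way; the heading and formula do not.

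**Conclusion.** The point holds. As designed, the trial can give a randomised estimate of expanded referral plus CHW against standard referral, and cannot give one of the CHW increment. Rejecting H02 would not show a CHW benefit. The control-arm wording of H02 and H03 contradicts their formulas and the arm description, H03's population wording contradicts its own heading and formula, and III.f omits a route that other sections describe.

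No numerical size attaches to this: it concerns what two secondary hypotheses can conclude. H01 and the main sample-size calculation are unaffected. The conclusion rests on CHW support having been given as IV.a.8 describes, to intervention-arm members only, and on PSU meaning the high-need, high-cost group for the population part of H03.

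**What to change.** 1. Restate Objective 2 and H02 as the package effect of expanded referral plus CHW versus standard referral among exchange members. Restrict both randomised arms, by the same rule, to CHW markets and dates, so that the comparison stays randomised. CHW ended before the allocation change of 10/01/2017, so the restricted set was randomised 50/50 throughout.
2. Label any estimate of the CHW increment, such as CHW against non-CHW markets, as non-randomised and exploratory. The choice of estimator can be left to the SAP; it would depend on comparable non-CHW exchange markets, which the protocol does not show.
3. In the text of H02 and H03, change the control model to standard CM/CC, to match the formulas and IV.a.8.
4. Define H03's population as members qualifying through high inpatient risk, spell out PSU wherever it remains, and reconcile III.f with the purpose section and IV.a.6.

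The cost is amended wording and one restricted analysis of data already collected. The downside is a more modest Objective 2 claim: the trial would report on the package, with the CHW's own contribution left as a hypothesis.
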